## 7. RESPONSE EVALUATION

Response must be evaluated through repetition of the CT scan of chest, abdomen and pelvis at week 6th and 12nd from treatment start and thereafter every 3 months.

Response will be codified by the Investigator according to the RECIST (Response Evaluation Criteria In Solid Tumours) guidelines version 1.1, summarised below.

### 7.1. Measurability of tumour lesions

At the baseline evaluation, the lesions will be defined as follows:

|                           |                                                                                                                                                                                                                                                                                                                                                                                                                                                                                                                           |
|---------------------------|---------------------------------------------------------------------------------------------------------------------------------------------------------------------------------------------------------------------------------------------------------------------------------------------------------------------------------------------------------------------------------------------------------------------------------------------------------------------------------------------------------------------------|
| A. measurable:     | 
Lesions which can be accurately measured on at least one dimension (the longest diameter must be recorded) and found to be <math>\geq 10</math> mm with CT scan or <math>\geq 20</math> mm with conventional techniques.
 
Lymph node found to be <math>\geq 15</math> mm in short axis with CT scan.
 
Note: All tumor measurements must be recorded in millimeters (or decimal fractions of centimeters).
                                                                                |
| A. non-measurable: | 
Lesions that are measurable but small (largest diameter <math>< 10</math> mm with CT scan or <math>< 20</math> mm with conventional techniques or pathological lymph nodes with <math>\geq 10</math> to <math>< 15</math> mm short axis).
 
Bone lesions, leptomeningeal disease, ascites, pleural/pericardial effusions, lymphangitis of skin or lung, and abdominal masses or organomegaly (that cannot be followed by CT or MRI).
 
Lesions that are located in previously irradiates areas.
 |

All measurements must be made using a centimetre rule or gauge.

All the baseline evaluations must be performed as close to the treatment start date as possible, and in all cases no more than 4 weeks earlier. If there is only one measurable lesion, the neoplastic nature of this lesion should be confirmed by cytologic or histologic examination.

### 7.2. Identification of "target" and "non-target" lesions

All measurable lesions up to a maximum of 2 lesions per organ and 5 lesions in total, representative of all involved organs, should be identified as **target lesions** and recorded and measured at baseline assessment. The target lesions should be selected on the basis of their size (lesions with the longest

diameter), trying to represent all the involved organs. In addition target lesions should be those that lend themselves to reproducible repeated measurements. It may be the case that, on occasion, the largest lesion does not lend itself to reproducible measurement in which circumstance the next largest lesion which can be measured reproducibly should be selected. The sum of the baseline diameters (longest for non-nodal lesions, short axis for nodal lesions) of all target lesions will be calculated, reported in the eCRF, and used as reference for defining the objective response.

All other lesions are identified as **non-target lesions** and must also be recorded at baseline assessment. Measurement of these lesions is not required, but the presence, absence, or the eventual unequivocal progression of each of them must be noted during the follow-up, at each scheduled restaging.

### 7.3. Evaluation of target lesion response

|                         |                                                                                                                                                                                                                                   |
|-------------------------|-----------------------------------------------------------------------------------------------------------------------------------------------------------------------------------------------------------------------------------|
| Complete response (CR): | disappearance of all the target lesions. Any pathological lymph nodes (whether target or non-target) must have reduction in short axis to <10 mm.                                                                                 |
| Partial Response (PR):  | reduction of at least 30% in the sum of diameters of the target lesions, compared to the baseline evaluation.                                                                                                                     |
| Progression (P):        | increase of at least 20% in the sum of diameters of target lesions and an absolute increase of at least 5 mm, compared to the lowest sum recorded since the start of the treatment, or the appearance of one or more new lesions. |
| Stable disease (SD):    | neither a sufficient reduction to be defined as PR, nor a sufficient increase to be defined as P.                                                                                                                                 |

### 7.4. Evaluation of non target lesion response

|                                                    |                                                                                                               |
|----------------------------------------------------|---------------------------------------------------------------------------------------------------------------|
| Complete Response (CR):                            | Disappearance of all non target lesions. All lymph nodes must be non-pathological in size (<10 mm short axis) |
| Non Complete Response / Non Progression (CR/nonP): | Persistence of one or more target lesions                                                                     |
| Progression (P):                                   | Appearance of one or more new lesions or indisputable, clear progression of an existing non-target lesion.    |

## 7.5. Evaluation of best overall response

The best overall response is the best response recorded from the start of treatment until disease progression/recurrence (taking the lowest measurement recorded since the start of treatment as reference for the progression).

| Target Lesions    | Non-Target Lesions                 | New Lesions | RECIST Response      |
|-------------------|------------------------------------|-------------|----------------------|
| CR                | CR                                 | No          | CR            |
| CR                | non-CR/non-P                       | No          | PR            |
| CR                | Not evaluated                      | No          | PR            |
| PR                | CR o non-CR/non-P or not evaluated | No          | PR            |
| SD                | CR o non-CR/non-P or not evaluated | No          | SD            |
| Not all evaluated | CR o non-CR/non-P                  | No          | Not evaluable |
| P                 | Any                                | Yes or No   | P             |
| Any               | P                                  | Yes or No   | P             |
| Any               | Any                                | Yes         | P             |

An overall deterioration in the state of health leading to a suspension of the treatment without evidence of progression will be defined as a "symptomatic worsening".

Patients who suspend treatment due to symptomatic worsening will be considered as non-responding.

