## 5. TREATMENT PLAN

### 5.1. Regorafenib treatment

Patients will receive regorafenib orally 160 mg once daily for the first 3 weeks of each 4-week cycle.

Treatment will be definitively stopped in case of disease progression, unacceptable toxic effects, motivated decision to stop the treatment by the treating physician, or refusal or withdrawal of consent by the patient.

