## 7.6. Reporting of results

All patients included in the study must be assessed for response to treatment, even if they are ineligible. Each patient will be assigned one of the following categories: 1) complete response, 2) partial response, 3) stable disease, 4) progressive disease, 5) early death from malignant disease, 6) early death from toxicity, 7) early death because of other cause, or 8) unknown (not assessable, insufficient data).

All patients will be included in the analysis of the response rate. Patients in response categories 4-8 will be considered as failing to respond to treatment.

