### 9.1 Primary endpoint

The rate of patients alive and not progressed at 6 months is the primary study end-point. This rate will be calculated by dividing the number of evaluable patients alive and not progressed after 6 months from study entry, by the number of enrolled evaluable patients. Exact 95% confidence intervals will be described.

The following will be considered as events:

- progression of disease at any date within 6 months from registration, according to RECIST criteria (including deterioration of clinical conditions that prevent radiological restaging);
- death for any cause within 6 months from registration;
- interruption of regorafenib due to adverse events followed by initiation of an alternative antineoplastic treatment within 6 months from registration.

If drug-related adverse events lead to definitive termination of regorafenib but the clinical condition of the patient does not require immediate switch to a different antineoplastic treatment, the patient can be followed according to protocol schedule and will be defined as success or failure according to the time of disease progression as above.

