### 9.2. Secondary endpoints

- Toxicity: for each patient and for each type of toxicity, the worst degree suffered during treatment will be described.
- Objective response rate: defined as the number of complete plus partial responses divided by the number of patients enrolled.
- Progression free-survival: defined as the time from registration to progression or death without progression, whichever occurred first. Patients without progression at the end of the study will be censored at the date of the last visit when eventual progression was verified.
- Overall survival: defined as the time from registration to the date of death due to any cause. Patients still alive at the end of the study will be censored on the date of the last information on vital status.
- Metabolic response: defined as a reduction  $\geq 50\%$  of SUVmax after 2 weeks of treatment.

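### Section 7.5 classifies a documented response followed by symptomatic worsening in two ways, and its response window does not close when another antineoplastic treatment starts

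*Protocol*

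**What the plan says.** Section 7.5 opens with the window: "The best overall response is the best response recorded from the start of treatment until disease progression/recurrence". After the response table it defines symptomatic worsening as a decline in general health that makes the patient stop treatment although progression has not been shown. It then adds: "Patients who suspend treatment due to symptomatic worsening will be considered as non-responding".

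Section 7.6 assigns every patient one of eight categories and says: "Patients in response categories 4-8 will be considered as failing to respond to treatment". PR is category 2. Symptomatic worsening is not among the eight.

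Section 9.2 gives the endpoint: "Objective response rate: defined as the number of complete plus partial responses divided by the number of patients enrolled". It does not refer to 7.5 and sets no cut-off of its own.

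On stopping and switching, Section 5.1 allows treatment to end without progression: "unacceptable toxic effects, motivated decision to stop the treatment by the treating physician, or refusal or withdrawal of consent by the patient". Section 5.5.1 bars other antineoplastic therapy only while the patient is on study treatment. Section 6.3 (Follow-up) asks for tumour status every 3 months and for data on later treatment. For the primary endpoint only, Section 9.1 counts as an event: "interruption of regorafenib due to adverse events followed by initiation of an alternative antineoplastic treatment within 6 months from registration".

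**The concern.** Two analysts who follow Section 7.5 to the letter can report different response rates from the same data. One keeps a PR that was recorded before the patient deteriorated. The other removes it, because the closing sentence makes no exception. Following the closing sentence drops a real response from the 9.2 count.

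The window also has only one stated end. Section 9.1 foresees patients who stop for toxicity and start another drug before progression, and it settles their status for the 6-month endpoint. No matching rule exists for response, so shrinkage produced by the next treatment can enter a rate meant to describe regorafenib.

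Objective response rate is a stated secondary measure of activity in a single-arm trial. If the choice is left until results are known, it becomes a post hoc decision on a small count.

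**Working it through.** **Plan's own figures.** The protocol states no expected response rate, so there is none to reproduce. The denominators come from the design in Section 4: 22 then 46 evaluable patients, p0 = 30%, p1 = 50%, continue with at least 8 of 22, positive with at least 18 of 46. An exact two-stage binomial calculation gives type I error 0.097 and power 0.905, within the stated 10% errors. The design is consistent and is not affected by this point.

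**Case A: response, then symptomatic worsening.** Take a patient with PR at weeks 6 and 12 who later stops because of declining health, with no progression shown.

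| Text | Result |
|---|---|
| 7.5, first sentence | The window is still open, since there is no progression. Best response is PR: responder |
| 7.5, last sentence | Treatment was stopped for symptomatic worsening: non-responder |
| 7.6 | PR is category 2, not a failing category. Worsening has no category, so nothing says which rule prevails |
| 9.2 | Counts CR plus PR. The result depends on which 7.5 sentence was applied |

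Section 9.1 treats deterioration that prevents restaging as progression. Borrowing that rule does not help. It would close the window at the deterioration, but the PR came earlier and would still be the best response under the first sentence.

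**Case B: stop for toxicity, switch, then shrinkage.** Take a patient who stops in cycle 1 for toxicity without progression, starts another antineoplastic treatment, and has a scan at week 12 showing at least 30% reduction from the study baseline (PR under 7.3).

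1. Section 7.5: no progression has occurred, so the window is open and PR can be recorded.
2. Section 9.2: no exclusion applies, so the patient can be counted.
3. Section 9.1: the same patient is a failure for the 6-month endpoint.
4. Whether a scan exists is unclear. Section 7 and footnote d of Table 6 run imaging without a stop at end of treatment, and 6.3 (Follow-up) asks for tumour status. Against this, the survival follow-up column of Table 6 lists survival status only, and footnotes r and s send patients who discontinue into survival follow-up, where telephone contact is acceptable.

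The text therefore permits the misattribution but does not make it certain.

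**Size.** Change in the rate per reclassified patient = 1/N.

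- N = 46: 1/46 = 2.2 points.
- N = 22 (stop after stage 1 as in Section 4): 1/22 = 4.5 points.

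This takes enrolled patients equal to evaluable patients. Section 9.2 divides by enrolled, so any enrolled patient who takes no drug makes the step slightly smaller. Section 9.3 gives 17 for the first stage, which conflicts with Section 4 and is a separate matter.

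Illustration with assumed responder counts, exact (Clopper-Pearson) 95% intervals, N = 46:

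| Responders | Rate | 95% CI |
|---|---|---|
| 1 | 2.2% | 0.1 to 11.5 |
| 2 | 4.3% | 0.5 to 14.8 |
| 3 | 6.5% | 1.4 to 17.9 |
| 4 | 8.7% | 2.4 to 20.8 |

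One or two reclassified patients change a low rate visibly in relative terms, but the intervals overlap heavily.

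**The case against.** **Next-line responses.** A reader might infer that the plan does count them. The documents do not support that. Section 7.5 is silent on new therapy, 7.6 speaks of response to treatment (most naturally the study drug), and Section 7 presents itself as a summary of RECIST 1.1. Patients who switch may have no scheduled RECIST scan. Section 9.1 offers continued follow-up on the protocol schedule to those who do not need an immediate switch, which suggests that switchers leave it. A cut-off at new therapy is also often left to an SAP. This reduces the point to what can happen. It does not remove it, because the protocol names one end to the window and 6.3 (Follow-up) still asks for tumour status.

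**Sections 7.5 and 9.1.** A reader might also see a contradiction between them. There is none: a patient can fail a 6-month endpoint and still be a responder. The comparison shows only that the switch was foreseen for one endpoint and not for the other.

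**Symptomatic worsening.** The closing sentence may have been meant only for patients without a recorded response. That is plausible, but it is not what the sentence says.

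**Size.** It is tempting to estimate a count. If 10 to 20% stopped for adverse events and a quarter to a half of them switched before progression, 46 x 0.10 x 0.25 = 1.2 to 46 x 0.20 x 0.50 = 4.6 patients would be exposed. None of these rates is in the protocol, and an exposed patient is not necessarily a responder.

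**Detectability.** Later treatment is recorded (6.3, Follow-up) and scans are collected for possible review of response (6.4). Either misclassification could be found and corrected at analysis, so the lack of a comparator does not hide it.

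**Conclusion.** The conflict within 7.5 stands on the text alone and needs no assumption: a documented CR or PR followed by symptomatic worsening is scored both ways, and 7.6 does not resolve it. The open window is a weaker, secondary point. A response first seen on another antineoplastic treatment can be counted, provided that a scan exists.

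The impact is minor. Each affected patient moves the response rate by 2.2 points at N = 46, or 4.5 points at N = 22. The number affected cannot be derived from the documents. Section 9 makes all analyses descriptive and response rate is a secondary endpoint, so the go/no-go rule, the primary endpoint and the sample size are untouched.

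**What to change.** In Section 7.5:

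1. Limit the symptomatic-worsening sentence to patients with no CR or PR documented before treatment was stopped.
2. End the best-response window at the earlier of progression or the start of any other antineoplastic treatment.

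In Section 9.2, refer the objective response rate to this definition.

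The cost is a few lines of endpoint wording. No new data are needed, since later treatment is already recorded under 6.3 (Follow-up), and no extra patients. The reported response rate may come out slightly different: the first change can only retain responses, and the second can only remove them. Agree the wording before response results are known.

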## 7.6. Reporting of results

All patients included in the study must be assessed for response to treatment, even if they are ineligible. Each patient will be assigned one of the following categories: 1) complete response, 2) partial response, 3) stable disease, 4) progressive disease, 5) early death from malignant disease, 6) early death from toxicity, 7) early death because of other cause, or 8) unknown (not assessable, insufficient data).

All patients will be included in the analysis of the response rate. Patients in response categories 4-8 will be considered as failing to respond to treatment.

## 8. ADVERSE EVENTS

### 8.1. Definitions

An **adverse event** is any untoward medical occurrence in a patient or clinical trial subject administered a medicinal product and which does not necessarily have a causal relationship with this treatment.

An **adverse reaction** is an untoward and unintended response to an investigational medicinal product related to any dose administered, judged by either the investigator or the promoter.

An **unexpected adverse reaction** (UAR) is an adverse reaction, the nature or severity of which is not consistent with the applicable product information (e.g. investigator's brochure for an unauthorized investigational product or summary of product characteristics for an authorized product).

A surgical procedure that was planned prior to the start of the study by any physician treating the subject should not be recorded as an AE (however, the condition for which the surgery is required may be an AE).

In the following differentiation between medical history and AEs, the term "condition" may include abnormal physical examination findings, symptoms, diseases, laboratory, or ECG results.

- Conditions that started before signing of informed consent and for which no symptoms or treatment are present until signing of informed consent will be recorded as medical history (eg, seasonal allergy without acute complaints).
- Conditions that started before signing of informed consent and for which symptoms or treatment are present after signing of informed consent, at unchanged intensity, will be recorded as medical history (eg, allergic pollinosis).
- Conditions that started or deteriorated after signing of the ICF will be documented as AEs.

A laboratory test abnormality that is considered to have a clinically relevant effect on the subject (eg, causing the subject to withdraw from the study, requiring treatment or causing apparent clinical manifestations, or judged relevant by the investigator) should be reported as an AE.

A **Suspected Unexpected Serious Adverse Reaction (SUSAR)** is an adverse reaction judged serious by either the investigator and/or the promoter, that is not consistent, either in nature or in severity, with the applicable product information.

### 8.2. Definition of a serious adverse event

A SAE is classified as any untoward medical occurrence that, at any dose, meets any of the following criteria:

- a. Results in death
- b. Is life threatening

The term ‘life threatening’ in the definition refers to an event during which the subject was at risk of death at the time of the event. It does not refer to an event that, hypothetically, might have caused death if it were more severe.

c. Requires in-patient hospitalization or prolongation of existing hospitalization

A hospitalization or prolongation of hospitalization will not be regarded as an SAE if at least one of the following exceptions is met:

- The admission results in a hospital stay of less than 12 hours
- The admission is pre-planned  
(ie, elective or scheduled surgery arranged prior to the start of the study)
- The admission is not associated with an AE  
(eg, social hospitalization for purposes of respite care)

However, it should be noted that invasive treatment during any hospitalization may fulfill the criterion of ‘medically important’ and as such may be reportable as an SAE, dependent on clinical judgment. In addition, where local regulatory authorities specifically require a more stringent definition, the local regulation takes precedence.

d. Results in persistent or significant disability/incapacity

Disability means a substantial disruption of a person’s ability to conduct normal life functions.

e. Is a congenital anomaly/birth defect

f. Is another medically important serious event as judged by the investigator

If disease recurrence leads to signs and symptoms that meet the criteria for seriousness (eg, hospitalization), the associated signs and symptoms may be reported as an SAE, but the underlying cause (that is, “recurrent disease” or “metastatic disease”) should not be reported as an SAE. In this case, recurrent or metastatic disease should be mentioned on the SAE form as an “alternative explanation.”

Additional primary cancers (including skin cancers) regardless of relationship to study treatment should be reported as SAEs.

An isolated laboratory abnormality that is assigned a severity rating of Grade 4, as defined in NCI-CTCAE v 4.0, is not reportable as an SAE unless the investigator assesses that the event meets standard International Conference on Harmonisation criteria for an SAE. Similarly, a baseline laboratory abnormality that is part of the disease profile should not be reported as an SAE when assigned a severity rating of Grade 4, as defined in NCI-CTCAE v 4.0.

